*Molecular endothelial function* will be characterized by measurement of a set of endomiRs which have been identified as key regulators of central pathways of endothelial cellular function by in vitro and in vivo animal and human models (Table 2). MiRNAs will be quantified from serum, because unlike plasma it is free from clotting factors which may skew the results. However, like plasma, serum analyses carry a risk for erythrocyte hemolysis, which is considerably smaller than the risk of contamination with intracellular miRNAs in whole blood samples. Hemolytic contamination of serum samples will be minimized by keeping the preprocessing time as short as possible and strictly adhering to standardized procedures of serum separation and storage. 7.5 ml blood will be collected per sample for separation and storage of 2—3.5 ml serum. The whole batch of 86 samples will be sent to QIAGEN for endomiR quantification blinded to participant and time point of sample acquisition. The miRCURY LNA miRNA SYBR Green PCR system based on wet-lab validated assays will be used enabling robust detection of desired miRNA sequences regardless of GC content and degree of similarity between different miRNAs. This system uses two LNA primers for PCR amplification and probe detection as a unique specificity-enhancing feature. Two RNA-spike-ins (UniSp6 and cel-miR-39-3p) will be used for internal control of sample hemolysis. As biological variability of serologic miRNA samples is considerably higher than technical variability, the main priority will be the number of biological replicates instead of technical replicates. Previous studies using these analyses protocols have produced excellent results with a single technical replicate [88, 89]. Controlling for sample volume and involving seven normalizer miRNAs will further minimize the risk of biased statistical effect estimates [56, 57].

**Table 2 Tab2:** List of selected endomiRs

MiRNA	Target protein	Pathophysiological effect
miR-10a (24)↓ miR-146a (25) ↓ miR-185 (26) ↑	NFκB ↑ NOX-4 ↑ GPx-1 ↓	Increased oxidative stress Increased oxidative stress Increased oxidative stress
miR-92a (27) ↓ miR-125a-5p ^a^ (28) ↑ miR-217 (29) ↑	TNF-α-receptor 1 ↑ eNOS ↓ SIRT-1 ↓	Reduced nitric oxide availability Reduced nitric oxide availability Reduced nitric oxide availability

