#### Statistical analyses

Pre-post-intervention changes of primary, secondary and tertiary outcomes will be quantified in the intervention- and control-group using paired samples t-test, and between-group differences will be analyzed with an analysis of covariance (ANCOVA). For the analyses of NLPE-related changes in endomiRs, we will conduct a principal component analysis to summarize the miRNA data into an uncorrelated component, which is plausible, because miRNAs involved in similar biochemical pathways typically show a high degree of correlation [56]. The significance level for all tests will be set at 5% and tests will be two-sided.

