#### Power calculation

The desired statistical power is ≥ 80%. However, there is no evidence about effects of NLPE on the primary outcome baFMD. Furthermore, one must keep in mind that the comparability of effects gained by an exercise intervention to those from similar previous studies is limited, as NLPE is essentially individualized, thus, difficult to reproduce. Conservatively, we assume that the effects of NLPE on baFMD will be leastways as high as those of MICT or HIIT, which are both essential features of NLPE. Based on results of comparable 8–12-week MICT- and HIIT-interventions [46, 101–109], a 2.67% mean pre-post-intervention change of baFMD (relative change = 48.6%) was assumed for the intervention group and no change for the control group. Analysis of covariance (ANCOVA) was used for effect estimation [110] assuming a correlation of *r* = 0.60 between baFMD values at T_0_ and T_2_ [46, 105]. We chose an allocation ratio of 2:1 between the intervention and control group, for economic reasons and to avoid exposing as little individuals as possible to the less effective control treatment. The loss of statistical power remains minimal compared to a set-up with a 1:1 ratio [111]. In summary, the necessary sample size for an 80% statistical power will be *n* = 39, with *n* = 26 of the participants being allocated to the intervention group and *n* = 13 to the control group. Estimating a 10% drop-out based on our own experiences and others [80], we intend to recruit a total of *n* = 43 participants.

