### Strengths and limitations – outcome measurements

Measurement of baFMD is very sensitive to investigator bias and to bias introduced by unstable environmental and situational conditions. An extensive training of the assessment staff before the start of measurements as well as strict adherence to detailed standardized operating procedures based on current guidelines [84] is crucial for valid results. Furthermore, the software-based semi-automatic quality control of baFMD measurements will be conducted by a trained person who will be blinded to the group allocation of the cases.

Although the measurement of SVA is less sensitive to investigator bias, the post-procedural manual quality control of the pictures, including the measurement of arteriolar and venular diameters, will also be made by an experienced assessor following standardized procedures [115].

To counteract the circadian, seasonal, and hemodynamic fluctuations that influence both clinical and molecular outcome measures, every measurement will be made under similar conditions (resting time, daytime, fasted, room temperature). However, seasonal fluctuations are imaginable. Hence, the effects could be slightly different, if the study was conducted in winter. However, this bias is most likely negligible with regards of the primary outcome, which is the “before-after” difference of the outcome parameters with “before” and “after” measurements being conducted within 2.5 months.

Thus far, only few studies have assessed effects of exercise on endomiRs, ECs, EPCs and sphingolipidome. In fact, there is no study assessing the effects of NLPE on these markers. However, the selection of target biomarkers and processing of samples brings various challenges and can ultimately lead to heavily flawed data and unreliable results. Most importantly, sample acquisition and processing need to be conducted timely and without any contamination, as pre-processing of serum for endomiR analysis can only be made within the first 60 min after sample acquisition.

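### The only haemolysis check named for the endomiR serum samples is a pair of spike-in RNAs, which reflect technical recovery and would not identify a haemolysed sample

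*Protocol article*

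**What the plan says.** The Protocol article, section Macro-, microvascular, molecular and cellular endothelial function, chooses serum for the microRNA work and accepts that "like plasma, serum analyses carry a risk for erythrocyte hemolysis". It ranks this risk well below that of intracellular contamination in whole blood.

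Prevention comes next: "Hemolytic contamination of serum samples will be minimized by keeping the preprocessing time as short as possible", together with standardized separation and storage. The section on circulating biomarkers adds immediate centrifugation and freezing at -80 °C. The section Strengths and limitations – outcome measurements adds a time limit: "pre-processing of serum for endomiR analysis can only be made within the first 60 min after sample acquisition".

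The only check on haemolysis in a sample is given in one sentence: "Two RNA-spike-ins (UniSp6 and cel-miR-39-3p) will be used for internal control of sample hemolysis". Seven normalizer miRNAs are also planned. They are not named, and their stated purpose is to limit biased effect estimates, not to find haemolysis.

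For quantification, "The whole batch of 86 samples will be sent to QIAGEN for endomiR quantification", with the laboratory blinded to participant and time point. The section Statistical analyses then plans a "principal component analysis to summarize the miRNA data into an uncorrelated component".

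**The concern.** The sentence gives the spike-ins a task that they cannot perform. A control for haemolysis must respond to something that comes from the participant's red cells. A spike-in comes from the laboratory.

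This is a misstatement, not an omission. The article did not leave the haemolysis check to another document; it named one, and the one named does not measure the stated problem.

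What is at stake is the endomiR outcome. If red-cell miRNAs enter some samples and shift several measured miRNAs together, that shared shift is variation that a principal component can absorb. The component would then carry sample quality as well as endothelial biology, and nothing in the stated plan would show it.

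**Working it through.** **1. What a spike-in can show.** The argument rests on the meaning of the term. A spike-in is added to the sample or the reaction, so its measured level reflects recovery through extraction, reverse transcription and PCR. The article uses the same idea for the sphingolipids: labelled internal standards are spiked into the extraction solvent, and concentrations are reported against the known amount of standard. Neither kind of added standard originates in the participant's red cells.

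**2. Does any other stated step detect haemolysis?**
- Short preprocessing, standardized separation and storage, immediate centrifugation and the 60-minute limit: prevention. They do not identify a sample in which prevention failed.
- Seven normalizer miRNAs: unnamed and not linked to haemolysis.
- Blinding of the laboratory: guards against assessment bias, not contamination.

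No absorbance reading, red-cell marker or haemolysis cut-off is named.

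**3. Number of samples.** "we intend to recruit a total of *n* = 43 participants", each sampled at T0 and T2: 43 × 2 = 86. This reproduces the stated batch of 86.

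**4. How much could it matter?** The document gives no haemolysis rate, number of affected miRNAs, shift size or inter-miRNA correlation, so all four are assumptions. The simulation used 86 samples (treated as independent) and 15 standardized miRNAs sharing one biological factor. Haemolysis was a common shift added to k of the 15 in 5%, 10% or 20% of samples. The result is R² between the first principal component and haemolysis status, averaged over 300 runs. With no haemolysis effect, R² is 0.01. The ranges below run over the three haemolysis rates:

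| miRNAs affected, shift | correlation 0.1 | correlation 0.3 | correlation 0.5 |
|---|---|---|---|
| 3 of 15, 1 SD | 0.02–0.05 | 0.02 | 0.01–0.03 |
| 3 of 15, 3 SD | 0.13–0.46 | 0.05–0.09 | 0.03–0.05 |
| 6 of 15, 1 SD | 0.06–0.20 | 0.03–0.09 | 0.02–0.05 |
| 6 of 15, 3 SD | 0.47–0.80 | 0.17–0.47 | 0.10–0.25 |

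Haemolysis dominates the component only when several miRNAs are strongly shifted and the miRNAs are otherwise weakly correlated. The article expects high correlation, which favours the right-hand column.

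**5. Cost as noise.** Assume that a fraction p of samples has its component score shifted by 2 SD. The variance factor is 1 + p(1 − p) × 2².
- p = 0.05 (about 4 of 86): 1.19, SD factor 1.09
- p = 0.10 (about 9 of 86): 1.36, SD factor 1.17
- p = 0.20 (about 17 of 86): 1.64, SD factor 1.28

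A comparison with 80% power (noncentrality 2.88, 36 degrees of freedom) would fall to 72.9%, 67.1% and 59.0%. The 80% is a reference value only: the article states power for baFMD and none for the endomiRs. The calculation also ignores the baseline adjustment in the planned ANCOVA.

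**The case against.** The strongest reply is that this is one laboratory sentence in a condensed article. Acceptance criteria for samples may sit in the full protocol or the laboratory's procedures, and their absence here is no finding. That stands for thresholds and exclusion rules. It does not rescue the sentence itself, which assigns the control to the wrong problem.

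A second reply is that the article does not define a spike-in or say when these two RNAs are added. That is true, and the point rests on the ordinary meaning of the term. The meaning is enough to say that the spike-ins are not a measure of red-cell release. Haemolysis might disturb extraction or amplification and so leave some trace in their signal; the documents do not say, and such a trace would not be specific.

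Four stronger readings are tempting and are not supported:
- A reader might infer that haemolysed samples will be kept in the analysis. Nothing says so; they would go unidentified by the stated check and could remain.
- A reader might infer that the plan treats haemolysis as the main contamination risk. It says only that "serum analyses carry a risk for erythrocyte hemolysis", and calls that risk the smaller one relative to whole blood.
- A reader might infer that contamination will drive the result because only the largest component is kept. The article does not say which component is used, and the simulation shows a weak effect in mild scenarios.
- A reader might infer a false positive for Hypothesis 2. Haemolysis unrelated to arm and visit mainly adds noise. Bias needs rates that differ by arm or visit, and the documents give no sign of this: handling is described as uniform and the laboratory is blinded to participant and time point.

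**Conclusion.** The sentence is wrong as written and should be corrected. The only haemolysis check named would not identify a haemolysed sample, and the preventive steps, though sensible, do not detect failures.

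The consequence is confined to the endomiR data: one secondary outcome and Hypothesis 2. The likely harm is noise and lost sensitivity, not a false effect. Its size is not derivable from the document. The simulated share of component variance (1% to 80% overall, 1% to 25% at correlation 0.5) and the power figures depend wholly on the assumed rates and shifts, and the simulation also assumes that the first component is the one analysed. The baFMD analysis, its power and the sample size of 43 are untouched.

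**What to change.** - Describe UniSp6 and cel-miR-39-3p as technical controls for extraction, reverse transcription and PCR.
- Name a haemolysis check on the stored serum that depends on red-cell content: absorbance at the haemoglobin peak, or the ratio of a red-cell-enriched miRNA to a stable one.
- Set the flagging threshold before unmasking.
- Repeat the component analysis without flagged samples as a sensitivity analysis, and report the number flagged by arm and visit, since a difference there is what would turn noise into bias.

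The cost is one absorbance reading per sample (86 readings) or one to two extra PCR assays per sample (86 to 172 assays), plus one repeated analysis. The samples are already stored and batched, so no visit or blood draw is added. If the full protocol or the laboratory's procedure already contains such a check, the change reduces to correcting the sentence and referring to it.

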#### Circulating biomarkers of systemic inflammation and cardiovascular risk

One 7.5 ml serum blood tube will be collected for the analysis of standard clinical biomarkers of systemic inflammation and cardiovascular risk, including fasting blood glucose, low- and high-density lipoprotein, total cholesterol, triglycerides and high-sensitive C-reactive protein.

Another 7.5 ml serum blood tube will be collected for the measurement of sphingolipid biomarkers of cardiovascular risk. Sphingolipid metabolites will be quantified using a stable isotope dilution liquid chromatography-tandem mass spectrometry approach. Plasma samples (200 uL) will be extracted with methanol spiked with 15 stable isotope-labelled internal standards. Extracts will be analyzed by Reversed-Phase Liquid Chromatography coupled to tandem mass spectrometry (RPLC—MS/MS) in positive ionization mode using 6495 triple quadrupole mass spectrometer interfaced with 1290 UHPLC system (Agilent Technologies) [91]. Data will be acquired in dynamic Multiple Reaction Monitoring mode with a total cycle time of 500 ms. Concentrations will be reported to the known concentration of corresponding (or analogous) internal standard using calibration curves. The analyses will be performed by the Metabolomics Unit, Faculty of Biology and Medicine, University of Lausanne.

All blood samples will be centrifuged immediately after acquisition, and the plasma aliquots will be frozen at a temperature of -80 °C until analysis of the whole batch after collection of the final sample.

#### Cardiorespiratory fitness

Peak oxygen consumption (V̇O2_peak_), the gold standard surrogate marker for cardiorespiratory fitness, will be measured by cardiopulmonary exercise testing. The standardized procedure has been conducted in an earlier study by the research team [92]. Spiroergometry will be conducted until maximal exertion using a cycle ergometer with an electromagnetic braking system (Ergoselect 200; Ergoline, Bitz, Germany). According to the participant’s predicted peak performance [93] one of the following ramp protocols will be selected (three-minute warm-up/ linear increment per minute): unloaded/ 7 W, 10 W/ 10 W, 20 W/ 15 W or 50 W/ 25 W. The three-minute recovery phase will be performed at the same wattage as the warm-up. By providing individual ramp protocols, an exercise duration between six and 18 min will be ensured [94, 95].

During exercise testing, gas exchange and ventilatory variables, serving as performance indicators, will continuously be analyzed breath-by-breath using a computer-based system (MetaMax 3B; Cortex Biophysik GmbH, Leipzig, Germany). V̇O2 (mL/min) and other variables will be acquired on a breath-by-breath basis and averaged over 10-s intervals. V̇O2_peak_ will be defined as the highest 30-s average of V̇O2 at any point during the test [96].

Further variables will be assessed to control for maximum exhaustion, including maximum blood lactate, subjective exhaustion and maximum heart rate. Capillary blood samples from the earlobe will be used to measure lactate concentrations at rest, maximum performance, and three minutes after termination of exercise testing. The analysis of blood lactate concentrations will be done via the SuperGL Ambulance (Hitado Diagnostic Systems, Moehnesee, Germany) immediately after the last blood sample is drawn. The Borg scale [97] will be applied at the end of the testing to assess maximum subjective effort. Objective load will be monitored by continuous measurement of heart rate and blood pressure (VaSera 1500, Fukuda Denshi Ltd., Tokyo, Japan) during all spiroergometric tests and during training. In order to detect and prevent any hazards to the participant’s health, a trained and certified sports scientist continuously supervises the examinations and training, and a physician is always available on request. Arterial oxygen saturation will be recorded continuously using a pulse oximeter (Masimo Corporation, Irvine, CA, USA). A standard 12-lead ECG will be obtained at rest, during the entire period of the exercise test, and for three minutes during recovery. In the absence of chest pain and electrocardiographic abnormalities, all tests will be continued until maximal exertion (i.e., volitional exertion, dyspnea, or fatigue).

To ensure optimal data validity, all tests will be performed strictly according to the current guidelines for exercise testing [96]. Therefore, the equipment will be calibrated in standard fashion with reference gas and volume calibration before each test. Every test will be preceded by a resting period of three minutes to reach steady-state conditions, which will be analyzed for the plausibility of V̇O2_peak_ and other gas variables. Pedaling cadence can be chosen by participants but will be required to be more than 60 rpm and the participants will continuously be encouraged to put in all possible effort.

#### Physical activity

Minutes per week of physical activity will be assessed as mean of the last 12 months via a 41-item questionnaire, and MET-hours per week will be calculated for light, moderate and vigorous physical activity. Participants will be eligible for participation if their physical activity is below the recommended amount of 150 min of moderate or vigorous physical activity, equaling less than 7.5 MET-hours per week [98].

#### Anthropometric measurements and questionnaires

General anthropometric sample characteristics comprising age, height, weight, smoking behavior, personal and family history of acute and chronic health conditions and current medication will be assessed at baseline and final appointments. Furthermore, body composition via bioelectrical impedance analysis (InBody770; InBody Co. Ltd., Seoul, Korea), resting heart rate/ rhythm via a 12-lead resting electrocardiogram (Cardio 100 ECG, Custo diagnostics, Ottobrunn, Germany), pulmonary function (spirometry) and resting blood pressure (VaSera 1500, Fukuda Denshi Ltd., Tokyo, Japan) will be measured.

The 7-item physical activity readiness questionnaire (PAR-Q) will be used for eligibility screening at the beginning of the baseline appointment [99].

To assess psychological effects of NLPE, the 19-item Profile-of-Mood-States questionnaire will be filled in by the participants at baseline and at the final appointment to monitor changes in overall mood that might be associated to the training [100].

#### Statistical analyses

Pre-post-intervention changes of primary, secondary and tertiary outcomes will be quantified in the intervention- and control-group using paired samples t-test, and between-group differences will be analyzed with an analysis of covariance (ANCOVA). For the analyses of NLPE-related changes in endomiRs, we will conduct a principal component analysis to summarize the miRNA data into an uncorrelated component, which is plausible, because miRNAs involved in similar biochemical pathways typically show a high degree of correlation [56]. The significance level for all tests will be set at 5% and tests will be two-sided.

#### Power calculation

The desired statistical power is ≥ 80%. However, there is no evidence about effects of NLPE on the primary outcome baFMD. Furthermore, one must keep in mind that the comparability of effects gained by an exercise intervention to those from similar previous studies is limited, as NLPE is essentially individualized, thus, difficult to reproduce. Conservatively, we assume that the effects of NLPE on baFMD will be leastways as high as those of MICT or HIIT, which are both essential features of NLPE. Based on results of comparable 8–12-week MICT- and HIIT-interventions [46, 101–109], a 2.67% mean pre-post-intervention change of baFMD (relative change = 48.6%) was assumed for the intervention group and no change for the control group. Analysis of covariance (ANCOVA) was used for effect estimation [110] assuming a correlation of *r* = 0.60 between baFMD values at T_0_ and T_2_ [46, 105]. We chose an allocation ratio of 2:1 between the intervention and control group, for economic reasons and to avoid exposing as little individuals as possible to the less effective control treatment. The loss of statistical power remains minimal compared to a set-up with a 1:1 ratio [111]. In summary, the necessary sample size for an 80% statistical power will be *n* = 39, with *n* = 26 of the participants being allocated to the intervention group and *n* = 13 to the control group. Estimating a 10% drop-out based on our own experiences and others [80], we intend to recruit a total of *n* = 43 participants.

#### Training intervention

The training will be conducted under supervision by experienced exercise coaches with at least a Bachelor’s degree in sports science. It will be conducted in groups of up to nine participants and will begin no more than two weeks after the baseline appointment.

The NLPE intervention will consists of two macrocycles of four weeks each, and the second cycle will be more intense than the first one. Every week, participants will attend three training sessions varying in duration and intensity. After the completion of the first macrocycle, another spiroergometry testing will be performed to readjust the intensity for the following training sessions. The exact amount of this increase will be defined individually for every participant according to their performance development (V̇O2_peak_ at T_1_) as well as individual readiness and appreciation assessed during the intervention period. This will ensure training in the target intensities throughout the whole study period and thus avoiding a common methodological limitation of many exercise trials.

Each session will start with a 15-min warm-up to minimize the risk of injury during training [112, 113]. Exercises for strength, dynamic flexibility and balance will also be included, which further support the training performance [114] and improve neuromuscular control [112]. In weeks 1 (habituation) and 5 (recovery), each session will consist of 30 min continuous cycling at moderate intensity of 40 – 50% peak oxygen consumption (V̇O2_peak_). Comparing to weeks 1 and 5, cycling duration will be longer in weeks 2 and 6 (high-volume for metabolic adaptation, i.e., mitochondrial density, improved anti-oxidant capacities) and intensities will be higher in weeks 3 and 7 (high-intensity for structural adaptation, i.e., remodeling of the extracellular matrix in the vascular wall). In weeks 4 and 8, both cycling duration and intensities will be higher (peak performance enhancement).

To ensure an adequate wash-out period without risking a loss of training effect, the final appointment, including another spiroergometry test of cardiorespiratory fitness, will take place three to seven days after the last training session. The participants will then receive standard recommendations regarding physical activity and a healthy lifestyle, based on the WHO’s guidelines for physical activity [79].

